## **Human Participants**

This protocol and the informed consent document and any subsequent modifications will be approved by the Ethics Committee of Dongzhimen Hospital Affiliated to Beijing University of Chinese Medicine (DZMEC-KY-2019-06). The consent form describes the purpose of the study, the procedures to be followed, randomized assignment into one of two groups, and the risks and benefits of participation. The decision regarding participation in the study is entirely voluntary. The patients have their right to retract participation in the study at any time without any penalty, or affecting the quality or quantity of their future medical care, nor loss of benefits to which the participant is otherwise entitled. All questions the patient may have will aim to be answered to the best of their ability by the research assistant. The investigator and the participant should both sign and date the consent form before the person can participate in the study.

### **(1) Possible risks and management**

Both Tuina and mPT should be performed by a professional and clinically experienced practitioner at a designated hospital. Local muscle and soft tissue pain may occur after treatment. To minimize the risk of muscle or joint soreness, the treatment progress will be implemented at interval days. Treatment associated with increased signs and symptoms of pain are suspended until symptoms resolve. If symptoms persist, the participant is referred to the patient's physicians. All patients are informed of any potential risks prior to their participation in any study procedures and are told that they are free to withdraw from the study at any time. Any situations occurred and management during the treatment should be recorded.

### **(2) Potential Benefits of the Proposed Research**

This study is a rigorously designed and implemented effective treatment for osteoarthritis of the knee. The treatment will contribute to relieving pain, improving function, and enhancing quality of life in KOA patients. Patients in the study, regardless of their random assignment, will receive treatment as recommended in current clinical practice or clinical guidelines, and will be treated throughout the whole process.

### Protocol with Amended Changes (May 26 and 28, 2019 Versions, registered in the website)

Before registering on the website, the original protocol (2018 version, described as above) was amended, which registered on May 26, 2019. And after registering the website, there was amended again on May 28, 2019. The summary of amended version and parts was summarized in the Table 3.

**Table 3. The summary of amended parts**

| Version              | Amend-Before                                                                                                                               | Amend-After                                                                                                                                                                                                                                                                                                                                                                                                                       | Reasons                                                                                                                                                                                                                                                                                                                                          |
|----------------------|--------------------------------------------------------------------------------------------------------------------------------------------|-----------------------------------------------------------------------------------------------------------------------------------------------------------------------------------------------------------------------------------------------------------------------------------------------------------------------------------------------------------------------------------------------------------------------------------|--------------------------------------------------------------------------------------------------------------------------------------------------------------------------------------------------------------------------------------------------------------------------------------------------------------------------------------------------|
| May 26, 2019 version | Number of days with restricted activities about KOA, Mental Health Index, Perceived Stress Scale, Tampa Scale for Kinesiophobia            | 30-second time chair rise test, Timed Up and Go Test Time, One Leg Standing Test,                                                                                                                                                                                                                                                                                                                                                 | Considering multiple-dimensions of evaluations of KOA, we changed the outcome questionnaires of activity ability, emotional and psychological stress to some physical performance-based measurements before registering on clinicaltrials.gov.                                                                                                   |
|                      | Assessment at baseline, week 4, and week 16.                                                                                               | Week 8 assessment of some important outcomes are added                                                                                                                                                                                                                                                                                                                                                                            | Due to long interval of 4-week and 16-week assessment                                                                                                                                                                                                                                                                                            |
|                      | KL (Kellgren-Lawrence) grade II or III in recent 6 months                                                                                  | KL (Kellgren-Lawrence) grade II or III in recent 3 months                                                                                                                                                                                                                                                                                                                                                                         | By shortening the timeframe for recent KL grade II or III, we can capture participants who are currently experiencing active disease and have more recently progressed to the specified grades. This change allows us to focus on homogeneous individuals who are more likely to exhibit ongoing symptoms and functional limitations due to KOA. |
| May 28, 2019 version | To test whether the participants are blinded successfully, all participants will be asked to guess which kind of acupuncture they received | To test whether the participants are blinded successfully, all participants will be asked to guess which kind of treatment they received                                                                                                                                                                                                                                                                                          | Error in filling in the statement of blinding assessment.                                                                                                                                                                                                                                                                                        |
|                      | Single blind (Outcome assessor)                                                                                                            | Double blind (Participant, Outcome assessor)
Patients only be informed that they received the manual therapies, but on information about whether traditional Tuina or Physical therapy, or no discussion of detailed manual therapy during the trial and treatment. Therapists will not be blinded due to delivering different treatment, but patients, evaluators, and statisticians will be blinded to the group assignment. | In the initial stage of trial, a test of blindness of participants had been conducted. The results showed feasible. The trial determined that participants was blinded.                                                                                                                                                                          |

The revised parts were highlighted in ***bold and Italic font*** as below and the information collection content and time frame showed in the Table 4.

## **Inclusion Criteria**

“KL (Kellgren-Lawrence) grade II or III in recent 6 months” changed to “***KL (Kellgren-Lawrence) grade II or III in recent 3 months***”.

## **Outcome Measures**

### **1. Primary Outcome Measure**

Change in Western Ontario and McMaster University Osteoarthritis Index (WOMAC)

[ Time Frame: Change from baseline at 4 weeks]

Self-report measure of WOMAC total.

### **2. Secondary Outcome Measure**

#### **(1) Change in WOMAC**

[ Time Frame: Change from baseline at ***8 weeks*** and 16 weeks]

Self-report measure of pain, stiffness, and physical function subscale for KOA.

#### **(2) Change in Numeric Rating Scale of Knee Pain**

[ Time Frame: Change from baseline at 4 weeks, ***8 weeks*** and 16 weeks]

Participants will rate their worst knee pain in the last 24 hours using an 11-point numeric pain rating scale with 0 representing “no pain” and 10 representing “ the worst pain imaginable”.

#### **(3) Change in Patient Global Assessment (PGA)**

[ Time Frame: Change from baseline at 4 weeks, ***8 weeks*** and 16 weeks]

The PGA rating is a 11-point Numeric Rating Scale (NRS) in which participants will rate the degree to which their knee condition has changed from the time treatment was initiated to the present. The participant responds to the following query: “Please rate your overall knee’s condition from the time you began treatment until now.” using an 11-point NRS with 0 representing “A very great deal better” and 10 representing “A very great deal worse”.

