**Table 4. Information collection content and time frame**

| Measures /Event                                 | Selection /baseline - 1 st | Week 4 - 2 nd        | Week 8 - 3 rd        | Week 16 - 4 th       |
|-------------------------------------------------|---------------------------------------|---------------------------------|---------------------------------|---------------------------------|
| Collection time range                    | Week -1 or Week 0                     | Within one week before or after | Within one week before or after | Within one week before or after |
| Informed Consent Form                    | X                                     |                                 |                                 |                                 |
| Basic Information                        | X                                     |                                 |                                 |                                 |
| WOMAC                                    | X                                     | X                               | X                               | X                               |
| NRS                                      | X                                     | X                               | X                               | X                               |
| PGA                                      | X                                     | X                               | X                               | X                               |
| OARSI Responder Criteria                 |                                       | X                               |                                 |                                 |
| Change in 30 second time chair rise test | X                                     | X                               |                                 |                                 |
| Change in Timed Up and Go Test Time      | X                                     | X                               |                                 |                                 |
| Change in One Leg Standing Test          | X                                     | X                               |                                 |                                 |

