### **7. Outcome Definitions**

**Primary Outcome** The change in the total Western Ontario and McMaster University Osteoarthritis Index (WOMAC) from baseline to 4 weeks

**Secondary Outcomes** The secondary outcomes covered pain, physical function, and patients' overall assessment of disease severity.

- **Pain Dimensions** WOMAC pain (the change between the baseline and 4, 8, and 16 weeks), the worst knee pain in the last 24 hour using NRS(the change between the baseline and 4, 8, and 16 weeks) ;

- **Function Dimensions** the average function of previous week using WOMAC function (the change between the baseline and 4, 8, and 16 weeks), WOMAC stiffness (the change between the baseline and 4, 8, and 16 weeks), 30 Second Time Chair Rise Test (the change between the baseline and week 4), Timed Up and Go Test Time (the change between the baseline and week 4), One Leg Standing Test (the change between the baseline and week 4);
- **Patients' overall assessment of disease severity:** the 12-item Short Form Health Survey (the change between the baseline and 4, 8, and 16 weeks), the patient global assessment (the change between 4, 8, and 16 weeks);
- **Criteria of Response Rate:** The OMERACT-OARSI responder criteria to assess the response rate of treatment for KOA at 4 weeks.
- **The blinding assessment**

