## 8. Analysis methods

We will use intention-to-treat analyses, analyses will be conducted by a statistician blinded to treatment allocation, with two-sided hypothesis tests. Changes from baseline will be presented for each group at each time point using the mean change and 95% confidence intervals.

**Primary outcome** Primary outcome will apply the repeated measures analysis of variance. Age, sex, BMI, baseline WOMAC score, medication as the covariates. The mean difference in change from baseline to 4 weeks of WOMAC total as the dependent variables, and group (Tuina group and mPT), time (baseline, week 4, 8 and 16), and the group  $\times$  time interaction as independent variables. The approximate normality and Mauchly's test of sphericity were examined. Then the interaction of group-interaction term was tested first. If significant, between-group differences at each time point were tested. If not significant, the treatment main effect was tested next.

**Secondary outcomes** For repeated measures of continuous outcome, including the subscale of WOMAC, NRS, SF-12 and PGA, will be estimated using the repeated measures analysis of variance, 30 Second Time Chair Rise Test, TUG and One Leg Standing Test will be applied with an independent t test for normal distribution, Mann-Whitney U test for unnormal distribution. And for categorical variables- responder criteria, will be compared across groups with the  $\chi^2$  tests or Fisher's exact test.

**Blinding outcome** Blinding assessment will apply the James blinding index with the blinding package of SAS software.

**Effect size** Effect size will be computed with mean group-difference/baseline SD; **MCID** The minimal clinically important difference (MCID) of WOMAC- total is set as 14%, which will be calculated with the change of baseline and the corresponding evaluation time point/baseline

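### The PGA is already a rating of change, yet the protocol defines its outcome as change from baseline and the SAP as change between follow-up visits; neither names the score itself as the endpoint

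*Supplement*

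**What the plan says.** **Instrument.** In the amended protocol, Secondary Outcome (3), "participants will rate the degree to which their knee condition has changed from the time treatment was initiated to the present". The question put to them is "Please rate your overall knee’s condition from the time you began treatment until now", answered from 0 (greatest improvement) to 10 (greatest worsening).

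**Protocol definition.** The entry is titled as a change in PGA. Its time frame begins "Time Frame: Change from baseline at 4 weeks" and goes on to 8 and 16 weeks.

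**Schedule.** Table 4 marks the PGA at the baseline visit, timed "Week -1 or Week 0", as well as at weeks 4, 8 and 16.

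**SAP definition.** Section 7 gives "the patient global assessment (the change between 4, 8, and 16 weeks". The other outcomes that section 7 defines as changes (WOMAC subscales, NRS, SF-12, performance tests) are measured from baseline. The PGA is not, and the baseline list in section 6 omits it.

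**SAP analysis.** Section 8 says that continuous repeated outcomes, "including the subscale of WOMAC, NRS, SF-12 and PGA, will be estimated using the repeated measures analysis of variance". It also says that each group's change from baseline will be presented at every time point, with no exception for the PGA.

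**The concern.** A transition rating asks the patient to do the subtraction: the answer at week 4 is the patient's own account of change since treatment started. Treating it like the NRS or WOMAC, which measure a state and need a baseline, goes wrong in one of two ways.

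- If a pre-treatment PGA is subtracted, the subtracted value answers a question that does not yet apply.
- If one follow-up PGA is subtracted from another, what remains is only the further change after the earlier visit. Any benefit already present at that visit drops out.

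The two documents also point to different reference points. An analyst could produce a baseline change, a between-visit change or a raw-score comparison and claim support for each. A fixed outcome definition is meant to remove that choice. At stake is the interpretability of one listed secondary outcome.

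**Working it through.** The documents give no PGA standard deviation, effect size or power, so there is no stated figure to reproduce. The inputs taken from them are 70 patients per arm (protocol, target number of participants) and a two-sided 5% level (SAP section 4). Effect sizes, baseline spread and persistence below are assumptions, in units of the follow-up SD of the PGA.

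**1. SAP wording taken literally, with week 4 as reference.** Let the arms differ by d at week 4, and let a share r of that difference remain at week 16. The difference in change is r·d − d = d(r − 1), while the true week-16 difference is r·d.

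| d | r | True week-16 difference | Difference in change, week 4 to 16 |
|---|---|---|---|
| 0.5 | 1 | 0.5 | 0 |
| 0.5 | 0.75 | 0.375 | −0.125 |
| 0.5 | 0.5 | 0.25 | −0.25 |
| 0.3 | 1 | 0.3 | 0 |
| 0.3 | 0.75 | 0.225 | −0.075 |
| 0.3 | 0.5 | 0.15 | −0.15 |

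In scale points: with one arm at 3 and the other at 5 at all three visits, the raw difference is 2 and the difference in change is 0 − 0 = 0. If part of the effect fades, the difference in change has the opposite sign to the difference that remains.

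**2. Protocol wording, follow-up minus baseline.** Suppose the baseline answer is unrelated to later ratings and its SD is k times the follow-up SD. The SD of the difference is then √(1 + k²), and

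power = Φ( d·√(70/2) / √(1 + k²) − 1.96 ), with √35 = 5.916.

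| k | SD of change | Power, d = 0.5 | Power, d = 0.3 |
|---|---|---|---|
| 0 | 1.000 | 0.841 | 0.427 |
| 0.25 | 1.031 | 0.819 | 0.406 |
| 0.5 | 1.118 | 0.754 | 0.355 |
| 1.0 | 1.414 | 0.552 | 0.240 |

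For example, at d = 0.5 and k = 1: 0.5 × 5.916 / 1.414 = 2.092, less 1.96 is 0.132, and Φ(0.132) = 0.552. The row k = 0 is the case in which every patient gives the same baseline answer. Both arms shift by a constant and nothing is lost. The row k = 1 doubles the variance, which is equivalent to halving the sample size. In no row is the expected difference between arms altered, because the baseline answer precedes treatment in both.

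**3. Raw scores.** A repeated measures analysis of the scores at weeks 4, 8 and 16 returns a group main effect of 2 points in the 3-versus-5 example, with no group-by-time interaction. Nothing is lost.

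**The case against.** The strongest reply is that the SAP may already intend the raw-score analysis. It assigns the PGA to repeated measures analysis of variance. The sequence written out for the primary outcome tests the interaction first and then, if that is not significant, the treatment main effect. Applied to raw PGA scores at three visits, this keeps a stable effect in full. The SAP also drops baseline from the PGA definition alone and leaves the PGA off its baseline list, as if it recognised a transition rating. No reference week and no subtraction step is named.

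On the protocol side, the original protocol carried the same change-from-baseline label although its Table 2 collected no baseline PGA, so there the label could not have meant subtraction. The summary of amendments does not mention the added baseline cell, which may be a slip.

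Much of this stands. A reader might infer that the plan removes the treatment effect, or that no planned analysis compares the arms on the rating itself. The documents do not support either. Full cancellation needs week-4 subtraction and an effect that stays constant afterwards, and the named method need not subtract at all. Nor do they show that precision will be halved, since that needs pre-treatment answers to vary as widely as post-treatment ones.

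The reply does not show that raw scores are the plan. The SAP's outcome definition speaks of change between visits, its presentation rule calls for change from baseline without exempting the PGA, and the time factor written out for the primary model includes baseline. The latest schedule does collect a baseline PGA that could be used in that way.

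**Conclusion.** The point holds as a faulty and inconsistent outcome definition. The instrument yields a change score, the protocol and SAP each define a further change on it with different reference points, and the score at each visit is nowhere named as the endpoint.

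The size depends on how the text is carried out. Under literal between-visit differencing, the effect reached by week 4 cancels in proportion to its persistence. Under baseline subtraction, the loss runs from nothing to a fall in power from 0.841 to 0.552 at an assumed 0.5 SD effect; this is added noise, not bias. With the repeated measures analysis run on raw scores there is no loss. These figures rest on assumed effects, spreads and independence, because the documents supply none for the PGA.

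The outcome is secondary. The WOMAC primary analysis and the sample size do not depend on it. The definition should still be corrected, because the text as written permits results that are hard to interpret and the remedy is simple.

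**What to change.** 1. Delete the baseline PGA mark in Table 4.
2. In the amended protocol, Secondary Outcome (3), and in SAP section 7, define the outcome as the PGA score at weeks 4, 8 and 16, and remove the references to change from baseline and change between visits.
3. In SAP section 8, exempt the PGA from the change-from-baseline presentation rule and report the mean score with its 95% confidence interval per group and visit.
4. In the same section, state that the repeated measures analysis already planned uses the raw PGA score, with time at three levels (weeks 4, 8 and 16) and no baseline or between-visit subtraction. No change of model is needed.

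The cost is a few lines of wording and one questionnaire fewer per patient.
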